Peers EXCEL provides an adapted diabetes self-management program for African Americans which includes group education sessions and one on one peer support. Group education includes the addition of new sessions that address misperceptions about diabetes and medicines influenced by racial discrimination/mistrust of providers, building self-efficacy, and provider communication. The additional one-on-one peer support occurs through race-congruent phone follow-up from other African Americans called Ambassadors. *Ambassadors* are African Americans with diabetes who are adherent to their medicines paired with African Americans with diabetes who are nonadherent (*Buddies*). Ambassadors’ interactions with their buddies focuses on addressing medicine and diabetes misperceptions, sharing experiences managing diabetes and medicines, and supporting self-efficacy and self-advocacy with their healthcare providers [31]. In the pilot trial of Peers EXCEL that examined feasibility and acceptability, we found the rates of recruitment were 80% for buddies and 100% for ambassadors. The rate at which the primary outcomes, medication adherence and A1C were retained was 75%. Participants mean completion rate was 13.4/17 of group sessions and phone calls with their ambassadors. About 84% of intervention phone calls were completed between the ambassadors and their buddies. We found no statistically significant differences in mean A1C and medication adherence. However, we found a clinically meaningful reduction (−0.7) in mean A1C at the inference point, 6-month follow up compared to the baseline. Based on the qualitative themes, participants reported the program to be culturally appropriate and acceptable with a perception of improved communication with their provider. They also reported that they learned strategies to assist with goal setting, and developed the confidence and motivation they needed for self-management [23].

Given these results, our next step is to conduct a pilot randomized controlled trial (RCT) of Peers EXCEL compared to HLWD to examine the feasibility and acceptability of the intervention and protocol and explore the benefits of the intervention in African Americans with uncontrolled diabetes using mixed methods.

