### 2.4. Participants

There are four groups of individuals involved in the pilot trial, but data analyses, and intervention outcomes will be collected principally from the HLWD and Peers EXCEL participants, i.e.,:

HLWD participants (control arm) (n = 12) –those who receive the HLWD content—who are African Americans with uncontrolled type 2 diabetes and nonadherent to their medicines.

Peers EXCEL participants (intervention arm) (n = 12)—those who receive the Peers EXCEL content—who are African Americans with uncontrolled type 2 diabetes and nonadherent to their medicines.

HLWD and Peers EXCEL participants’ inclusion criteria include: (1) Adults who are aged between 18 and 90 years old who are African American/Black with type 2 diabetes, and can speak and/or read English, (2) Self-report they have been prescribed at least one oral or injectable diabetes medicine, (3) Will be located in in the area geographically during the study period, (4) Self-reported medication nonadherence on the DOSE Nonadherence scale and (5) Most recent A1c value is ≥7.5% based on information collected by the research team at point of care A1C testing.

Exclusion criteria include: (1) If currently participating in a diabetes management or program focused on medication adherence, (2) Self-reported, schizophrenia, dementia, and untreated bipolar disorder or active substance use disorder (not having been in recovery for three or more months) (3) Older adults who report experiencing severe hypoglycemia in the past, and required medical assistance or the administration of glucagon

We will elicit feedback from individuals serving as Ambassadors and HLWD facilitators:

Peers EXCEL ambassadors (n = 4)—that is, those who relay intervention content via phone—who are African Americans with controlled diabetes (A1C ≤ 7.5%) and are adherent to their medication. Other inclusion criteria include (1) Adults who are aged between 18 and 90 years old who are African American/Black with type 2 diabetes, and can speak and/or read English, (2) Self-report they have been prescribed at least one oral or injectable diabetes medicine, (3) Being diagnosed with type 2 diabetes for at least one year (4) Will be located in the area geographically during the time of the study, (5) Being able to support another peer and track the phone conversations, and (6) Being prepared to attend all meetings and sessions focused on training them for their roles

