### 2.7. Data Analysis

Quantitative. Paired *t*-tests (or a non-parametric corresponding test such as Wilcoxon rank sum test) will examine pre- vs. post-intervention changes in participant’s A1C, medication adherence, and other psychosocial outcomes across groups to examine a signal of change. We will use descriptive statistics to calculate ambassadors’ feasibility measures, HLWD and Peers EXCEL participants, including ambassador recruitment, ambassador attrition, and extent of ambassador participation in sessions related to their training and intervention. We will consider the recruitment approach as feasible if: there is recruitment of all ambassadors and participants as planned, attrition for both ambassadors and participants is less than or equal to 10%, and the rate for ambassador and participant participation is equal to or higher than 80%.Qualitative. Interviews and focus groups will be audio-recorded and transcribed. Research assistants will code transcripts inductively using NVivo v 12 and conduct qualitative content analysis [56]. Qualitative content analysis will be used to organize the themes. All transcribed transcripts will be read initially for data immersion, taking time to read all the data line by line. Then, the codes and themes will be developed and organized with a conceptualization of how the themes are all lined together in the data. We will compare all themes exploring if there are similarities, interconnections, and/or differences across all themes. We will continue all data analysis until we get to theoretical and there are no more new dimensions in the data [57,58,59]. We will establish rigor of the data and explore the trustworthiness of the data analysis process using Lincoln and Guba (1985) four general criteria [60]. These are credibility, transferability, dependability, and confirmability. For credibility, two research assistants will code the transcripts independently—investigator triangulation (i.e., multiple coders involved in the data analysis), discuss similarities and divergences, and reach agreement by consensus before the final data interpretation. We will member check with participants interested in being part of the process to confirm if our interpretation is salient/credible—to check for resonance with participant experiences. Confirmability, objectivity/potential congruence between researchers. To ensure our findings are based on our participants’ responses and not any personal motivations or personal bias from our research team, after coding, all similarities and divergences will be discussed. Agreement will be reached on codes before results interpretation. Transferability, the scope to which results are applicable to other contexts. We will purposively sample individuals with varied intervention experiences and use detailed descriptions to show how the research study’s findings may be applicable in other contexts, circumstances, and situations. Dependability—the ability to achieve consistent findings if the study is done as described. We will create and report a detailed audit trail of our process throughout the analysis process. Documents and field notes data will also be analyzed using content analysis.Mixed. After analyzing the quantitative and qualitative data separately, the mean score differences, statistical effect sizes, and themes will be compared in the context of the feasibility, acceptability, and primary and secondary outcomes. The results from both phases will be interpreted together in a joint display to aid a meta-inference of the merged results.

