### 3.1. Limitations

Despite this study’s potential strengths, there are some potential limitations and anticipated challenges. Our research team has planned for how to address these potential issues, when possible. For example, it is likely that peer matching will not work initially, possibly because of the unavailability of an ambassador. If this occurs, we will use our established protocol from our prior studies for reassignment. Though not experienced in our prior work, recruitment retention of ambassadors may be an issue. To minimize this possibility, we will initially match ambassadors and their peer participants on a 1:3 ratio and allow 1:4 if needed. Recruiting enough African Americans may be challenging. Therefore, the research team has developed strong partnerships with several community partners in the study location. Early in the process of designing the study, the research team met with the community partners to present the study idea and plan and received their commitment where they would assist with recruiting participants. Another potential issue we could face is retaining the study participants during the study period. To assist with increasing participant retention, the research team will have check-in phone calls with each participant once every week. We currently plan to have face-to-face group sessions for the intervention. If a virtual approach is needed, both the HLWD and Peers EXCEL programs have experience being held virtually.

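### The feasibility rule in section 2.7 reports a retention or participation shortfall as a failed recruitment approach, and its 10% attrition limit allows no loss among four ambassadors

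*Protocol article*

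**What the plan says.** Section 2.7 sets three conditions, joined by 'and', for calling the recruitment approach feasible:

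- Recruitment: "there is recruitment of all ambassadors and participants as planned".
- Attrition: "attrition for both ambassadors and participants is less than or equal to 10" percent.
- Participation: "the rate for ambassador and participant participation is equal to or higher than 80" percent.

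There is no intermediate zone, and no reason is given for the thresholds.

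Other sections bear on the rule:

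- Section 2.4 plans 12 participants per arm and 4 ambassadors: "Peers EXCEL ambassadors (n = 4").
- Section 3.1 foresees that ambassadors may be hard to recruit or keep, and responds: "we will initially match ambassadors and their peer participants on a 1:3 ratio and allow 1:4 if needed".
- The Abstract and section 2.6.2 list recruitment, intervention acceptability, intervention adherence and retention as distinct feasibility domains.
- The Introduction gives the earlier single-programme pilot's results. On recruitment it says: "we found the rates of recruitment were 80% for buddies and 100% for ambassadors". On outcome data it says: "The rate at which the primary outcomes, medication adherence and A1C were retained was 75" percent. On participation it says: "Participants mean completion rate was 13.4/17 of group sessions and phone calls with their ambassadors". It adds that about 84% of the phone calls were completed.

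**The concern.** Feasibility is the first study aim, and section 2.7 holds the only numerical criterion for it. Two features of that criterion look wrong.

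First, the label does not match the content. The verdict is on recruitment, but two of its three conditions measure what happens after recruitment. A study that enrols everyone and then loses three participants would be reported as having an infeasible recruitment approach. Acceptability has no condition in the rule at all.

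Second, a percentage limit is applied to a group of four. The rule then fails on a single ambassador loss, which is an event the matching plan is designed to withstand.

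At stake is the headline feasibility statement that the planners of the larger trial will read. It could point them to the wrong domain, or turn on one or two people.

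**Working it through.** The article derives none of its thresholds, so there is no calculation of the plan's to reproduce. The checks below use its own inputs.

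**1. The limit as whole people.** Find the largest k with k/n ≤ 0.10.

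| Group | n | Losses allowed | One more loss |
|---|---|---|---|
| Ambassadors (section 2.4) | 4 | 0 | 1/4 = 25% |
| Participants (Abstract) | 24 | 2 (8.3%) | 3/24 = 12.5% |

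**2. Against the contingency in section 3.1.** At 1:3, 12/3 = 4 ambassadors are needed. At 1:4, 12/4 = 3 are enough. Losing one ambassador can therefore be covered in delivery, but it gives 25% attrition and fails the rule.

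**3. Chance of meeting the attrition part.** Assume losses are independent with true rate p in both groups.

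- Participants: P(X ≤ 2) = Σ C(24,k) p^k (1−p)^(24−k), for k = 0, 1, 2.
- Ambassadors: P(no loss) = (1−p)^4.

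| True p | ≤2 of 24 lost | 0 of 4 lost | Both |
|---|---|---|---|
| 5% | 0.884 | 0.815 | 0.72 |
| 10% | 0.564 | 0.656 | 0.37 |
| 25% | 0.040 | 0.316 | 0.01 |

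For p = 10% the participant terms are 0.0798 + 0.2127 + 0.2718 = 0.564, and 0.564 × 0.656 = 0.370.

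**4. What a pass would show.** Exact (Clopper-Pearson) 95% confidence intervals are 1% to 27% for 2/24 lost and 0% to 60% for 0/4 lost.

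**5. The earlier pilot against the rule.**

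| Part | Pilot figure | Limit | Result |
|---|---|---|---|
| Participant recruitment | 80% (denominator not stated) | all as planned | short, if a share of target |
| Ambassador recruitment | 100% | all as planned | met |
| Participant attrition | 100 − 75 = 25% of outcome data not retained | ≤10% | short, if outcome data stand in for attrition |
| Ambassador attrition | no figure | ≤10% | not assessable |
| Participation, sessions and calls | 13.4/17 = 78.8% | ≥80% (0.80 × 17 = 13.6) | short by 0.2 of a contact |
| Calls alone | about 84% | ≥80% | met |

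**6. The label.** Suppose all 24 participants and 4 ambassadors are recruited, participation is above 80%, and 3 participants are lost. The recruitment condition is fully met, yet the rule returns an infeasible recruitment approach.

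**The case against.** The strongest reply is that the rule is only a summary. Sections 2.6.1 and 2.7 report recruitment, attrition and participation descriptively, and section 2.6.2 uses qualitative data to explain metrics that lag. A reader of the full results would see which part failed. That stands, and it limits the harm: information is not lost, but the stated verdict is still mislabelled.

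A second reply is that absorbing a loss in delivery and counting it as a shortfall are compatible. That also stands. Section 3.1 does not strictly contradict section 2.7. Even so, a limit written as 10% that means zero should be a deliberate choice, and nothing in the article shows that it is.

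Third, a reader might infer that chance dominates the rule. The documents do not support that in general. Any cut-off performs poorly when the true rate sits on it. Away from it the participant limit discriminates: ≤2/24 is met 88% of the time at 5% attrition, 11% at 20% and 4% at 25%. The wide intervals come from the group sizes, not from the rule.

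Fourth, a reader might infer that the earlier pilot fails on every count. It does not. Ambassador recruitment and call completion met the limits, and section 3.1 says ambassador recruitment and retention problems had not been experienced. Participation missed narrowly, and the 80% and 75% figures need the assumptions shown above. Setting targets above past performance is also legitimate, and section 3.1 adds weekly check-in calls to support retention.

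Finally, a reader might take the rule as a go/no-go gate for the larger trial. No section says so. The Abstract says that the results will inform that trial.

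**Conclusion.** The concern holds in a limited form. As written, the rule attaches a recruitment verdict to retention and participation results, which conflicts with the article's own separation of domains. Its attrition limit means no loss among 4 ambassadors and at most 2 among 24 participants. These conclusions need only the stated numbers, taking the participant limit over both arms together.

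The probabilities of 37% (true attrition 10%) and 72% (true attrition 5%) assume independent losses and the same rate in both groups. At a true rate of half the tolerated limit, the attrition part alone would therefore still fail in about 28% of such trials (1 − 0.72).

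The pilot comparison is supporting evidence only. Its participant-level figures fall short of each part, subject to the unstated denominator and the use of outcome-data retention as a proxy, and no reason is given for thresholds stricter than that experience. The point is worth correcting, but it does not undermine the design.

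**What to change.** Reword the rule in section 2.7 as follows:

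- Give a separate feasibility verdict for each named domain, and judge recruitment on recruitment figures only.
- State the attrition limits as counts, participants out of 24 and ambassadors out of 4, and say what counts as attrition. Report each with an exact 95% confidence interval.
- Reconcile the ambassador limit with the 1:4 matching in section 3.1. Either say that one loss covered by re-matching is acceptable, or say that zero loss is intended and why.
- If graded bands are wanted, the sponsor should choose and justify them. The documents supply no basis for particular cut-offs, and looser ones have a price: accepting up to 4 of 24 losses would be met 91% of the time at 10% attrition, but also 25% of the time at 25%.

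The cost is the rewording of one rule and a few extra intervals. Sample size, visits and data collection do not change. If one ambassador loss is tolerated, that criterion becomes slightly less ambitious.

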
## 3. Expected Results

It is expected that the intervention trial protocol will be feasible to implement and be acceptable to African Americans with type 2 diabetes. Finally, we expect that participants who complete the Peers EXCEL intervention will have a signal of change in mean A1C that is clinically meaningful (≥0.6 reduction) compared to participants randomized to HLWD at baseline, 2 months, and 6 months. The primary outcome is to see a reduction in A1C, while the secondary outcome will be to determine if there is an improvement in medication adherence, assessed via self-report in the Peers EXCEL participants compared to the HLWD participants at 6 months.

### 3.1. Limitations

Despite this study’s potential strengths, there are some potential limitations and anticipated challenges. Our research team has planned for how to address these potential issues, when possible. For example, it is likely that peer matching will not work initially, possibly because of the unavailability of an ambassador. If this occurs, we will use our established protocol from our prior studies for reassignment. Though not experienced in our prior work, recruitment retention of ambassadors may be an issue. To minimize this possibility, we will initially match ambassadors and their peer participants on a 1:3 ratio and allow 1:4 if needed. Recruiting enough African Americans may be challenging. Therefore, the research team has developed strong partnerships with several community partners in the study location. Early in the process of designing the study, the research team met with the community partners to present the study idea and plan and received their commitment where they would assist with recruiting participants. Another potential issue we could face is retaining the study participants during the study period. To assist with increasing participant retention, the research team will have check-in phone calls with each participant once every week. We currently plan to have face-to-face group sessions for the intervention. If a virtual approach is needed, both the HLWD and Peers EXCEL programs have experience being held virtually.

### 3.2. Implications and Future Research

This pilot randomized controlled trial has the potential for further understanding if a culturally tailored intervention integrating evidence-based diabetes self-management content with race-congruent peer support improves hemoglobin A1c, medication adherence, and other psychosocial and behavioral barriers to medication adherence compared to a standard evidence-based diabetes self-management program. Findings from this study may address an unmet critical need to provide culturally tailored educational content and peer support to a patient population historically beset by harms related to uncontrolled diabetes. Building upon a widely used, evidence-based program, we anticipate that the intervention has the potential to be disseminated nationally in the United States to reduce diabetes mortality and morbidity in African Americans. Future research can expand on this study by testing the effectiveness of the culturally tailored intervention in a large powered randomized controlled trial.

## 4. Conclusions

This protocol paper described the design and proposed pilot randomized controlled trial to examine the acceptability, feasibility, and signal of benefit of a culturally adapted self-management intervention for African Americans with uncontrolled type 2 diabetes. To our knowledge, this is the first study to examine whether an intervention with amplified focus on medication adherence and culturally tailored race-congruent peer support combined with evidence-based diabetes self-management group education optimizes glycemic control and medication adherence among African Americans.

## Figures and Tables

**Figure 1 pharmacy-11-00002-f001:**
[figure not shown]
The Randomization Process.

**Table 1 pharmacy-11-00002-t001:** Intervention Content for Intervention Arm (Peers EXCEL) and Control Arm (HLWD).

Intervention Content	Weeks											
	1	2	3	4	5	6	7	8	9	14	19	24
Group sessions of beliefs about diabetes, provider mistrust and pharmacist communication	*	*										
Group sessions of diabetes self-management, healthy eating, problem solving, exercise, communication, medication, cultural experiences, discussing diabetes with family			*	*	*	*	*	*				
			#	#	#	#	#	#				
Referral to community health worker, if requested									*	*	*	*
									#	#	#	#
Peer-based phone call support									*	*	*	*

* Intervention Arm (Peers EXCEL Program); # Control Arm (Healthy Living with Diabetes Program).

**Table 4 pharmacy-11-00002-t004:** Measures for Study Outcomes.

Construct	Measure	Baseline	2 Months	6 Months
Primary Clinical Outcome				
Blood glucose	Hemoglobin A1c (A1C)	×	×	×
Secondary Study Outcome				
Medication adherence	DOSE-Nonadherence survey [46,47], extent of nonadherence domain	×	×	×
Other Measures				
Diabetes-health beliefs	Brief Illness Perception Questionnaire [48]	×	×	×
Beliefs about diabetes medicines	Beliefs about Medicines Questionnaire [35]	×	×	×
Diabetes and medication self-efficacy	Diabetes Empowerment Scale—Short Form [49] Self-Efficacy for Adherence to Medication Use Scale [50]	×	×	×
Diabetes distress	Diabetes Distress Scale (DDS-2) [51]			
Patient-provider communication	Patient’s Perceived Involvement in Care Scale [52]	×	×	×
Patient activation	Patient Activation Measure [53]	×	×	×

## Data Availability

Not applicable.
